### **8.5 Criteria for Suspension of Further Injections**

If a dose of vaccine is considered significantly reactogenic (see below), dose escalation and/or additional vaccinations will be suspended until reviewed by the Medical Monitor, SMC and study sponsor (SVI). Any recommendation of the Medical Monitor and SMC to resume or suspend further injections (either for an individual participant, an entire dose cohort, or all dose cohorts) will be communicated in writing to the sponsor and Principal Investigator. All communications from the SMC will subsequently be forwarded by the investigators to the CPqRR and GWUMC IRBs.

The following criteria will be used to define significant reactogenicity (note that in Part II of the study, these apply to both the *Na*-GST-1 vaccines and Butang® vaccine, as these criteria will be applied in advance of any consideration of unblinding):

- a. One or more participants experience an SAE (as defined in **Section 8.1.2** in this protocol) that is determined to be possibly, probably, or definitely related to the vaccine (as defined in **Section 8.2.3** in this protocol), **OR**
- b. One or more participants experience a hypersensitivity reaction (a Grade 3 allergic reaction, as defined in **Appendix D**) that is possibly, probably or definitely related to the vaccine, **OR**
- c. One or more participants in a single dose cohort experience an objective physical finding or laboratory abnormality of Grade 3 or higher (with the exception of isolated Grade 3 erythema or swelling), as defined in **Section 8.2.2** in this protocol, that is determined to be probably or definitely related to the vaccine. **OR**

- d. Two or more participants in a single dose cohort experience a Grade 2 or higher safety laboratory abnormality or Grade 3 clinical AE that is possibly, probably or definitely related to the vaccine.

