**Table 4: Assessment of Adverse Event Severity**

| Adverse Event                         | Grade                 | Severity                                                                                                                                                                                                                                                                  |
|---------------------------------------|-----------------------|---------------------------------------------------------------------------------------------------------------------------------------------------------------------------------------------------------------------------------------------------------------------------|
| Pain at injection site                | 0
1
2
3
4 | None
Easily tolerated, does not interfere with activity
Repeated use of non-narcotic pain reliever for > 24 hours or interferes with daily activity
Any use of narcotic pain reliever or prevents daily activity
Emergency room (ER) visit or hospitalization |
| Tenderness at injection site          | 0
1
2
3
4 | None
Mild discomfort to touch
Discomfort with movement
Significant discomfort at rest
ER visit or hospitalization                                                                                                                                             |
| Erythema at injection site            | 0
1
2
3
4 | < 25 mm
25 mm - 50 mm
51 mm - 100 mm
> 100 mm
Necrosis or exfoliative dermatitis                                                                                                                                                                              |
| Induration/swelling at injection site | 0
1
2
3
4 | <25 mm
25 mm - 50 mm and does not interfere with daily activity
51 mm - 100 mm or interferes with daily activity
>100 mm or prevents daily activity
Necrosis                                                                                                  |
| Fever (oral)                          | 0
1
2
3
4 | <38.0°C
38.0°C - 38.4°C
38.5°C - 38.9°C
39.0°C – 40.0°C
>40.0°C                                                                                                                                                                                               |

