### 8.2.3 Association with Receipt of the Study Vaccine

All AEs will have their possible relationship to study vaccine assessed using the following terms:

- Definite: Clear-cut temporal association, and no other possible cause.
- Probable: Clear-cut temporal association and a potential alternative etiology is not apparent.
- Possible: Less clear temporal association; other etiologies also possible.
- Unlikely: Temporal association between the AE and the vaccine or the nature of the event is such that the vaccine is not likely to have had any reasonable association with the observed illness/event (cause and effect relationship improbable but not impossible).
- Not Related: The AE is completely independent of vaccine administration; and/or evidence exists that the event is definitely related to another etiology.

The degree of certainty with which an AE can be attributed to administration of the study vaccine will be determined by how well the event can be understood in terms of one or more of the following:

1. The event being temporally related with vaccination or reproduced on re-vaccination.
2. A reaction of similar nature having previously been observed with this type of vaccine and/or formulation.
3. The event having often been reported in the literature for similar types of vaccines.

All local (injection-site) reactions will be considered definitely related to vaccination.

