## 8.3 Adverse Event Reporting

All SAEs will be reviewed by a study physician, recorded on the appropriate SAE form, and followed through to resolution or stabilization by a study physician. All SAEs will be reported by email, telephone or fax within 1 working day of notification of the SAE occurrence to the Principal Investigator, to all of the following:

- Sponsor (Office of Vaccine Operations, Sabin Vaccine Institute): [contact], [contact]
- Centro de Pesquisa René Rachou Ethics Committee: [contact], [contact]
- GWUMC Institutional Review Board (IRB): [contact], [contact]

Following notification from the investigator, SVI as the sponsor of the investigational product, will report events that are both serious and unexpected that are possibly, probably, or definitely related to the vaccine, to the FDA and ANVISA within the required timelines: fatal and life-threatening events within 7 calendar days (by phone, fax, or internet) and all other SAEs in writing within 15 calendar days. All SAEs not listed as possibly, probably, or definitely related will be reported to the FDA and ANVISA at least annually in a summary format.

All AESIs will be reported to Sponsor and to the FDA and ANVISA according to the same procedure as for reporting SAEs, and according to the same timelines as described above.

All local and systemic reactions not meeting the criteria for “serious adverse events” will be captured on the appropriate case report form (CRF). These events will be followed to resolution. Grade 3 adverse events deemed definitely or probably related to vaccination will be reported by email or fax within 15 working days of the Principal Investigator becoming aware of the event, to the Sponsor and the Safety Monitoring Committee.

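### Two suspension criteria in 8.5 and the 8.3 report name Grade 3 without adding 'or higher', so a worse (Grade 4) non-serious event can trigger less than a Grade 3 one

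*Protocol*

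**What the plan says.** Section 8.2.2 grades adverse events from 0 to 4, with Grade 4 meaning potentially life threatening. Section 8.5 then lists four criteria, any one of which suspends escalation or further vaccination pending review:

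- **(a)** one related serious adverse event (SAE);
- **(b)** one participant with "a hypersensitivity reaction (a Grade 3 allergic reaction", as graded in Appendix D, at least possibly related;
- **(c)** one participant in a cohort who "experience an objective physical finding or laboratory abnormality of Grade 3 or higher", probably or definitely related, "with the exception of isolated Grade 3 erythema or swelling";
- **(d)** "Two or more participants in a single dose cohort experience a Grade 2 or higher safety laboratory abnormality or Grade 3 clinical AE", at least possibly related.

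Section 8.3, in the paragraph on reactions that are not serious, adds: "Grade 3 adverse events deemed definitely or probably related to vaccination will be reported by email or fax within 15 working days". The recipients are the Sponsor and the Safety Monitoring Committee (SMC).

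Criterion (c) and the laboratory limb of (d) are open-ended upwards. Criterion (b), the clinical limb of (d) and the 8.3 sentence name Grade 3 alone. No section states that a Grade 4 event also counts as Grade 3.

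**The concern.** A suspension rule should never react less to a worse event. As worded, this one can. Two participants in a cohort with a Grade 3 symptom suspend dosing, but the same two with that symptom at Grade 4 may not. A single possibly related Grade 3 allergic reaction suspends dosing, but a non-serious Grade 4 one may not.

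This is the first human use of the antigen (section 1.9), and GLA-AF had not yet been given to humans (section 1.11). The earlier hookworm antigen was halted in an endemic area because of immediate hypersensitivity (section 1.3). The automatic triggers in 8.5 are there so that suspension in such a setting does not depend on someone's judgment on the day.

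**Working it through.** The protocol states no figure on this point, so the check is a literal trace of the criteria.

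**Step 1. Can a Grade 4 clinical event be non-serious?** Table 4 gives Grade 4 for injection-site pain as "Emergency room (ER) visit or hospitalization". Headache, nausea, tenderness, myalgia, arthralgia and urticaria are graded the same way. Of the 12 systemic rows in Appendix D, 11 define Grade 4 like this, including hypersensitivity; the exception is vasovagal episode, where Grade 4 does not apply. Section 8.1.2 requires an overnight stay for the hospitalization item and immediate risk of death for the life-threatening item. It leaves the important-medical-event item to judgment. A same-day emergency room visit can therefore be Grade 4 and not an SAE.

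**Step 2. Two worked cases.**

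- *Pain.* Two participants in one cohort go to an emergency room for injection-site pain and leave the same day. Both are Grade 4. Relatedness is fixed by section 8.2.3: "All local (injection-site) reactions will be considered definitely related to vaccination". Criterion (a) is not met unless the events are judged medically important. Criterion (c) is not met because pain is not an objective finding. Criterion (d) is not met because neither event is Grade 3. At Grade 3 the same two events meet (d). One Grade 3 plus one Grade 4 gives a count of 1, so (d) is missed again.
- *Fever rated possibly related.* Two fevers of 39.5°C are Grade 3 (39.0 to 40.0°C) and meet (d). Two of 40.5°C are Grade 4 (above 40.0°C) and do not. Criterion (c) does not help, because it needs probable or definite relatedness.

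**Step 3. All combinations.** Take five event types by three relatedness levels. Objective local findings are always definite under 8.2.3, which removes two cells: 5 × 3 − 2 = 13. All events are taken as non-serious, so (a) is off. Each cell was tested with one event (Grade 3, or Grade 4) and with two (3+3, 3+4, 4+4). A cell is inverted if a higher grade triggers less than a lower one.

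| Event type | Possible | Probable | Definite |
|---|---|---|---|
| Symptom only | inverted, (d) | inverted, (d) | inverted, (d) |
| Objective systemic finding | inverted, (d) | covered by (c) | covered by (c) |
| Allergic, with objective signs | inverted, (b) | covered by (c) | covered by (c) |
| Objective local finding | – | – | covered by (c) |
| Laboratory | covered by (d) | covered by (c), (d) | covered by (c), (d) |

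Inverted cells: 3 + 1 + 1 = 5 of 13. With *or higher* added in (b) and the clinical limb of (d), the count is 0 of 13.

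For symptoms, of the three pairings 3+3, 3+4 and 4+4, only the mildest meets (d). In a Part I cohort of 6, even six non-serious Grade 4 symptoms give a literal (d) count of 0. With the fix the count is 6.

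**Step 4. Rows of Table 4 (12).**

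| Status of a non-serious Grade 4 event | Rows | Number |
|---|---|---|
| Escapes | pain, headache, nausea, myalgia, arthralgia | 5 |
| Arguable (could be an examination finding) | tenderness | 1 |
| Escapes only if rated possible | fever, urticaria, rash | 3 |
| Caught by (c) | erythema, induration | 2 |
| Not counted (Grade 4 involves hypotensive shock, likely serious) | vomiting | 1 |

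**Step 5. The 8.3 report.** A non-serious, probably or definitely related Grade 3 event has a dated report to the Sponsor and SMC. The sentence names no such report for a non-serious Grade 4 event.

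**The case against.** The strongest reply is that this is a slip of wording. The authors almost certainly meant Grade 3 or higher, and few monitors would read a safety rule as excluding worse events. A participant with a Grade 4 event will usually have passed through Grade 3 as well: a fever of 40.5°C was earlier 39.5°C, and pain that leads to an emergency room has usually prevented daily activity. The drafters may also have expected clinical Grade 4 events to be handled as SAEs. The intent is probably as described. But passing through Grade 3 helps only if events are not graded by their maximum, and the protocol does not settle that. Section 8.1.2 does not make every Grade 4 event serious.

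The exception in (c) is a weaker guide than it first appears. Reading its bare Grade 3 inclusively would seem to exempt Grade 4 erythema, defined as "Necrosis or exfoliative dermatitis". It can fairly be answered that necrosis is no longer isolated erythema. Even so, the list uses the bare grade and the open-ended form in the same clause, so they cannot safely be treated as the same.

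Other safeguards exist in both Parts. The Medical Monitor and SMC must be kept aware of new safety information (8.4.1, 8.4.2). SMC approval is needed before the next dose concentration (8.4.2). The Medical Monitor may hold the study at any time (8.10). A hypersensitivity reaction bars that individual from further doses (8.7), and a Grade 4 allergic reaction may well be judged serious. These reduce the practical risk, but they rest on judgment or general duties. By its terms, the written approval does not cover second and third doses within a cohort, or the step from Cohort 7 to Cohort 8, which adds GLA-AF at the same 10 µg dose.

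Same-day emergency visits look less likely in Part II, given the remote site with a study clinician in or near it. The 13 cells are an unweighted classification, and three of the five inversions are one event type at three relatedness levels. The placing of rash is debatable, since its Grade 4 is necrosis. All of this limits the reach of the point without removing it.

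**Conclusion.** The point holds. Read literally, a related, non-serious Grade 4 clinical event can meet no suspension criterion where the same event at Grade 3 would, in 5 of 13 combinations of event type and relatedness, and it falls outside the dated report in 8.3. This assumes that an event is classified by its maximum grade and that the important-medical-event judgment is not exercised.

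The gap is narrow: symptoms at any relatedness, and objective systemic findings and allergic reactions rated only possibly related. The cell count shows where the rule inverts, not how often it would matter; no frequency can be given. It is a wording defect, but it sits in the decision threshold of a first-in-human suspension rule and should be corrected.

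**What to change.** Amend three sentences:

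- 8.5(b): a Grade 3 *or higher* allergic reaction;
- 8.5(d), clinical limb: Grade 3 *or higher* clinical AE;
- 8.3: Grade 3 *or higher* adverse events.

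Leave the erythema and swelling exception in 8.5(c) at Grade 3 only, so that Grade 4 local findings stay inside that criterion.

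The cost is two words in each of three sentences, made by protocol amendment. In operation it may add an occasional pause for review or an extra report.

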## **8.6 Treatments That Could Potentially Interfere with Vaccine-Induced Immunity**

The following criteria will be checked at each visit. If any are reported during the study, the participant will be excluded from receiving further doses of the study vaccine and will not be included in the immunogenicity evaluations after the time of exclusion. The participant will, however, be encouraged to remain in the safety evaluation for doses already received.

1. Use of any investigational drug or investigational vaccine other than the study vaccine during the study period.
2. Administration of chronic (defined as more than 14 days) immunosuppressants or other immune-modifying drugs up to 30 days after the last dose of vaccine. (Topical and nasal steroids are allowed.)
3. Administration of immunoglobulins and/or any blood products up to 30 days after the last dose of vaccine.

## **8.7 Criteria for Suspension of Injections**

The following criteria will be checked prior to each immunization and are contraindications to further immunization. However, the participant will be encouraged to remain in the safety evaluation for doses already received.

1. Hypersensitivity reaction following administration of a study vaccine.
2. Pregnancy, as determined by a positive urine  $\beta$ -hCG.
3. Occurrence of any other condition, which in the view of the investigators or Medical Monitor could jeopardize the safety of the study participant or may complicate interpretation of the safety or immunogenicity data.

## **8.8 Criteria for Deferral of Injections**

The following adverse events constitute grounds for deferral of vaccine administration at that point in time; if any one of these occurs at the time scheduled for vaccination, the participant may be vaccinated at a later date, within the allowable time interval specified in **Section 7.6** of this protocol, or withdrawn at the discretion of the investigator. The participant must be followed until resolution or stabilization of the event as with any AE. If the participant is withdrawn from the study, he/she will be encouraged to remain in the safety evaluation for the duration of the study.

1. Oral temperature  $> 38.0^{\circ}\text{C}$  at the time of vaccination will warrant deferral of immunization until fever and symptoms resolve.
2. Any other acute condition that in the opinion of the investigator poses a threat to the individual if immunized or that may complicate interpretation of the safety of the vaccine following immunization.

Such individual(s) will be followed until the symptoms resolve or the window for immunization expires. No further vaccination will be performed if the participant does not recover (oral temperature  $\leq 38.0^{\circ}\text{C}$  and/or lack of symptoms) within the originally scheduled vaccination time interval. The participant, however, will be followed for safety and immunogenicity evaluations. If the individual meets any of the above criteria for deferral on the day of first immunization, as an alternative to deferral of vaccination, the investigator may instead elect to exclude the participant from enrollment in the study. Eligible alternates will then be vaccinated instead.

## **8.9 Criteria for Withdrawal of an Individual Participant from the Study**

A participant will not be considered to have completed the trial if any of the following reasons apply. However, any participant who has received at least one dose of vaccine will be encouraged to remain in the safety evaluation for the duration of the study. Should a female participant become pregnant during the course of the study, she will not receive further doses of vaccine, but will be followed for the duration of the pregnancy.

1. *Research terminated by sponsor or investigator* – applies to the situation where the entire study is terminated by the sponsor or investigator for any reason.
2. *Withdrawal of consent* – applies to a participant who withdraws consent to participate in the study for any reason.
3. *Noncompliant with protocol* – applies to a participant who does not comply with protocol-specific visits or evaluations, on a consistent basis, such that adequate follow-up is not possible and the participant's safety would be compromised by continuing in the trial. Additionally, this applies to a participant who is lost to follow-up and cannot be located.
4. *Develops an adverse event* - applies to a participant who is withdrawn from the study due to an adverse event, serious or otherwise.
5. *Other* – is a category used when previous categories do not apply, and requires an explanation.

## **8.10 Breaking the Study Blind**

As outlined in **Section 4.4**, Part II of the study will be double-blinded until all study participants have completed their Day 140 visit, after which the investigators will be unblinded. During the double-blinded part of the study, a study participant's randomization code may be unblinded only for safety purposes. This is very unlikely to occur, as once a vaccine is administered, knowing which vaccine was given is unlikely to influence the medical management of an AE. This procedure is therefore exceptional and any decision to unblind will be discussed with the sponsor, the Principal Investigator, the Medical Monitor, and the SMC. If deemed necessary for urgent safety reasons, the Medical Monitor, in consultation with the SMC (if possible in a timely manner), may unblind a specific participant without revealing the study blind to the investigators or the Sponsor. Any unblinding will be thoroughly documented. It is to be emphasized that the Medical Monitor may put the study on hold at any time and discuss with the SMC. The decision to completely unblind or permanently stop the study prior to Day 140 will take the form of a formal recommendation by the SMC to the study Sponsor. The Principal Investigator must then notify the IRBs of this decision.

In the event that the investigators come to know the study code prior to final unblinding, the Principal Investigator must notify the Sponsor immediately. The reasons will be documented by the Principal Investigator and added to the study file.

Unblinding of the investigators will be done after all study participants have completed the Day 140 visit and upon authorization of the Sponsor. This will take place only after monitoring and verification of cGCP compliance by SVI, and after all safety and primary immunological results (i.e., antigen-specific IgG antibody levels as determined by ELISA) have been entered and the databases locked.

## **9 DATA COLLECTION AND MONITORING**

### **9.1 Source Documentation and Case Report Forms**

Complete source documentation (clinical evaluations and test results) will be collected for every study participant for the duration of the study. In addition, supplementary documents (laboratory test reports, supplementary hospital or medical records, etc.) may form part of the source documentation for a study participant. CRFs will be used to record study-specific data for enrolled participants. The Principal Investigator is responsible for the accuracy and completeness of the data reported in the CRFs and the source documents. Data reported in the CRFs that is derived from source documents should be consistent with source documents and the discrepancies should be explained.

### **9.2 Study Documentation**

Study-related documentation will be completed as required by the IRBs, the sponsor, and regulatory authorities. Continuing review documentation will be submitted by the Principal Investigator to the IRBs on the anniversary date of initial review as specified by each IRB. An annual report will be submitted by the sponsor to the FDA within 60 days of the anniversary date that the IND for *Na-GST-1/Alhydrogel*® was submitted.

